### Database security, quality assurance, and ethics

We have established a secure database to combine data from each source. The same combination of manual review, quality control reports, and built-in logic checks that has been used to ensure data quality for UMN LD survey responses will be used for all surveys in this study to ensure the integrity of the data. This study has been approved by the Institutional Review Boards of the University of Minnesota and the Mayo Clinic.

### Statistical considerations

#### Primary control group and matching algorithms

Although the REP control matching algorithm outlined in Sect. 2.4 matches on age at index date and race/ethnicity, there may be important differences between the LDs and potential REP controls on other characteristics. We plan to rematch LDs to these potential REP controls based on other clinical characteristics. Although laboratory data is nearly complete in the LDs (due to the extensive donor evaluation), these data are less complete among otherwise healthy potential controls. Indeed, it is possible that measurement of some characteristics (e.g., serum creatinine), particularly among young, otherwise healthy individuals, may indicate suspicion of disease. Thus, requiring potential controls to have complete laboratory data may lead to selection bias. However, including potential controls with missing laboratory values may lead to detection bias as some of these controls may have an unrecognized underlying disease. We will consider several different sets of characteristics to match on to create control cohorts which vary between minimizing detection bias and minimizing selection bias. This will allow us to determine the variability/range of incidence rates for each outcome that are dependent on how the controls are matched to donors. A prior study assessing risk of CKD with kidney stones had this same challenge of missing serum creatinine levels in the REP, but found reasonably consistent findings in analyses that minimized detection bias versus analyses that minimized selection bias [147].

For the **primary analysis**, we consider controls for whom we can ascertain BMI, systolic and diastolic blood pressure, use of anti-hypertensive medications, smoking history, and known normal serum creatinine, normal blood urea nitrogen (particularly relevant in the 1960s where serum creatinine testing may not have been done), or normal urine protein (with no abnormal values for any of these 3 tests) identified within 10 years prior to the index date (minimize detection bias as we avoid any controls who may have had unrecognized kidney disease due to absence of kidney function testing). We additionally will attempt to include family history of CKD at the index date (either through chart review or from survey results) as a factor in the matching. Urine protein tests allowed are comprehensive (urine dipstick protein, 24 h urine protein, 24 h urine albumin, urine protein to creatinine ratio, urine protein to osmolality ratio, and urine albumin to creatinine ratio). However, we expect most will be urine dipstick proteins. Normal is defined using the reference range at the time of the test. Our preliminary data suggested that younger controls will often not have a baseline serum creatinine level, though about half will have a urine protein assessment. Since most kidney disease in younger adults is proteinuric, a normal urine protein test in younger adults (age < 50 years) will be considered sufficient for inclusion in this analysis.

We plan to use optimal, sparse 1:k matching with refined covariate balance[148, 149] to ensure that the patients who are in each group (donors and controls) are as similar as possible based on age, sex, race/ethnicity, BMI, systolic and diastolic blood pressure, hypertension, smoking history, and family history of CKD. Briefly, this method allows one to exactly match on a small number of covariates (in this sense the method is sparse because it does not consider all possible matched pairs). The matching algorithm allows the near fine balance on discrete covariates between the intervention and control group (this means the distribution of the covariate is the same in the two groups but individuals may be matched to others with different levels of the covariate, i.e., frequency matching). An advantage of this approach is that it allows prioritization for balance on certain covariates over others. Finally, individuals are matched to minimize the overall difference between individuals using Mahalanobis distance or difference in propensity score (in this sense the match is optimal). The number of matched controls will depend on the number of potential controls with the available data. For each cohort of matched controls, we will assess the quality of matches by 1) computing the standardized difference of means for each covariate, as well as two-way interactions and squares and 2) for continuous covariates, examining quantile–quantile (QQ) plots, which compare the empirical distributions of each variable in the donor and control groups. Covariates for which there is an imbalance (e.g., standardized mean difference greater than 0.1) may be discretized and matched either exactly or to achieve near fine balance. Because matching is part of the design phase (as opposed to the analysis phase), we can repeat the matching several times until an acceptable balance is achieved without inflating type I error rates. If not enough controls with a matching characteristic (e.g., family history of CKD) are identified for matching to LDs, then the presence of the characteristics in both LDs and controls will be corrected for with multivariable adjustment for the analyses in predicting outcomes. Given that causal analysis is a rapidly developing field we will additionally consider state-of-the-art methodologies for determining optimal matches as new discoveries are made in this field.

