**Methods:**

The goal of the Minnesota Attributable Risk of Kidney Donation (MARKD) study is to compare the long-term (> 50 years) outcomes of living donors (LDs) to contemporary and geographically similar controls that are well-matched on health status. University of Minnesota (n = 4022; 1st transplant: 1963) and Mayo Clinic LDs (n = 3035; 1st transplant: 1963) will be matched to Rochester Epidemiology Project (REP) controls (approximately 4 controls to 1 donor) on the basis of age, sex, and race/ethnicity. The REP controls are a well-defined population, with detailed medical record data linked between all providers in Olmsted and surrounding counties, that come from the same geographic region and era (early 1960s to present) as the donors. Controls will be carefully selected to have health status acceptable for donation on the index date (date their matched donor donated). Further refinement of the control group will include confirmed kidney health (e.g., normal serum creatinine and/or no proteinuria) and matching (on index date) of body mass index, smoking history, family history of chronic kidney disease, and blood pressure. Outcomes will be ascertained from national registries (National Death Index and United States Renal Data System) and a new survey administered to both donors and controls; the data will be supplemented by prior surveys and medical record review of donors and REP controls. The outcomes to be compared are all-cause mortality, end-stage kidney disease, cardiovascular disease and mortality, estimated glomerular filtration rate (eGFR) trajectory and chronic kidney disease, pregnancy risks, and development of diseases that frequently lead to chronic kidney disease (e.g. hypertension, diabetes, and obesity). We will additionally evaluate whether the risk of donation differs based on baseline characteristics.

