### Limitations of prior work

In a review of studies reporting increased long-term risk for LDs, Janki et al. identified that both the Norwegian study reporting an increased risk of CVD, mortality, and ESKD, and the US study reporting increased risk of ESKD, selected non-donor control populations that were healthier than the donors, resulting in an over estimation of risk [103]. In addition, the definition of ESKD differed between donors and non-donors in the US study, potentially biasing the results. A meta-analysis of the cardiac studies concluded that there was no increase in CVD disease or mortality in LDs [104]. For the two studies identifying an increased risk of ESKD among LDs, the number of events was small, and there have been additional concerns about methodology, including: controls were non-contemporaneous and from a different geographic location; lack of renal function assessment for controls at the date corresponding to the date of donation; and concerns about the choice of statistical methods [105–115].

A key limitation in existing studies is that there was no determination of family history of chronic kidney disease (CKD) or ESKD for controls. In the Norwegian study, all 9 donors who developed ESKD were first-degree relatives of the recipient; in the US study, 83 of the 99 who developed ESKD were related to the recipient. Numerous studies in the general population have shown that individuals related to a person with ESKD have an increased risk of ESKD [116–122]. Wainright et al., using the Organ Procurement and Transplantation Network (OPTN) database, reported that LDs who were first-degree relatives of the recipient had significantly increased risk of ESKD (highest in identical twins) compared to LDs who were distant relatives or were unrelated to the recipient [123].

There have only been a few studies of pregnancy risk postdonation [100–102, 124, 125]. Studies have been limited by low numbers of events, and the design has generally been restricted to a before-and-after study design which may result in an over estimation of risk.

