To address these calls to action and limitations of existing studies, the Minnesota Attributable Risk of Kidney Donation (MARKD) study will compare the long-term risks for LDs from UMN and Mayo Clinic (first donation in 1963 and up to 60 years of follow-up) to the long-term risks for contemporaneous, geographically similar, healthy matched controls from the Rochester Epidemiology Project (REP). By reviewing medical records, we additionally plan to identify a subset of controls from the REP with known normal kidney function at a date corresponding to the date of donation and known family history of CKD and be able to match controls to LDs on these important risk factors. Consequently, we will provide the best data to date to inform prospective candidates of the long-term risks of kidney donation.

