#### Control groups for sensitivity analysis

In addition to the set of controls selected for the primary analysis, we will consider additional broader groups from the REP from which to match. As in the primary control group, we plan to use sparse optimal 1:k matching to match REP patients in these groups to LDs.

i)REP patients for whom we can ascertain BMI, systolic and diastolic blood pressure, diagnosis of hypertension, smoking history, and normal renal function (normal serum creatinine, normal blood urea nitrogen, or normal urine protein). This group does not consider family history of CKD.ii)REP patients for whom we can ascertain BMI, systolic and diastolic blood pressure, diagnosis of hypertension, and smoking history with no known abnormal renal function (abnormal serum creatinine, abnormal blood urea nitrogen, or abnormal urine protein). This group does not consider family history of CKD or require renal function testing to have been done.iii)A group that does not consider family history of CKD, require renal function testing to have been done, or consider clinical characteristics (however, patients with known contraindications to donation would have already been excluded and those with known abnormal renal function will still be excluded).iv)Additionally, we will construct control groups using matching algorithms as close as possible to those used in previous studies[55, 56] to assess the effect of different matching criteria on the rates of each outcome.

For each control group (primary and sensitivity cohorts) we match to LDs, we will estimate the incidence rate of each outcome.

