A major innovative aspect of our study is our contemporaneous healthy matched control cohort. Unlike prior studies, we will more clearly delineate matched controls that reflect the health status of donors just prior to the date of donation. This will be accomplished by identifying controls known to be healthy and with normal renal function at the index date (matched to donation date) who are from the same geographical region of residence (Upper Midwest) as donors, and by obtaining granular data on controls to allow for optimal matching of controls to LDs on key characteristics (including family history of CKD).

Longitudinal follow-up of both LDs and REP controls provides detailed, uniquely available health information on events preceding ESKD and mortality. In contrast to previous studies, we will compare LDs and healthy-matched REP controls on the much more common intermediate endpoints (e.g., low GFR; CVD) that occur before ESKD or death. Additionally, we will be able to study outcomes of LDs who develop new comorbidities late after donation (e.g., obesity, hypertension, DM, early or late GFR < 45 ml/min/1.73m^2^, proteinuria). This will provide information about whether the impact of these comorbidities differs for those with 1 vs. 2 kidneys. That is, we will be able to assess if differences in long-term outcomes between donors and controls are mediated by differences in postdonation comorbidities.

We will be among the first studies to evaluate modifiers of the effect of donation on ESKD and mortality. There have been several studies of risk factors for developing ESKD in the donor population. However, these identified risk factors are also risk factors for ESKD in the general population. By using well-matched REP controls, we will be able to assess the effect of donation for “ideal” LDs and for LDs who, at donation, have risk factors for CKD. That is, ours will be among the first studies to test if the attributable risk of an outcome with kidney donation is modified by clinical and demographic factors (e.g., age, BMI, smoking, donation eGFR).

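### A kidney test up to 10 years old qualifies a primary control, the article claims normal kidney function at the index date, and no stated analysis varies the age of the test

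*Protocol article*

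**What the plan says.** **The rule** (Protocol article, Primary control group and matching algorithms). A primary control must have a normal creatinine, a normal BUN, or "normal urine protein (with no abnormal values for any of these 3 tests) identified within 10 years prior to the index date". For controls under 50, "a normal urine protein test in younger adults (age < 50 years) will be considered sufficient for inclusion in this analysis"; the article expects most urine protein tests to be dipsticks.

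**The claim.** The last paragraph of the Background promises "a subset of controls from the REP with known normal kidney function at a date corresponding to the date of donation". The Discussion presents the control cohort as a major innovation, achieved by "identifying controls known to be healthy and with normal renal function at the index date".

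**The criticism of others.** Limitations of prior work lists among the faults of two earlier ESKD studies a "lack of renal function assessment for controls at the date corresponding to the date of donation".

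**The sensitivity analyses.** Control groups for sensitivity analysis opens with "we will consider additional broader groups from the REP from which to match" and lists groups i to iv. Statistical analyses details adds a repeat of the analyses in REP controls with at least 5 years of medical history before index.

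**The concern.** Donors had an extensive evaluation, and Table 1 reports their creatinine as measured at donation. A control may enter on a single result obtained years earlier, with no later kidney test. That is knowledge of past kidney health, not of kidney health at time zero, and it falls short of the standard that the article sets for other studies.

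Disease that began between the test and the index date would leave some controls less healthy than the donors they are matched to. Their later events would count as background risk, so the risk attributed to donation would tend to come out too low. That direction agrees with the study's hypothesis of small, clinically insignificant differences, so a reader of a near-null result will want to know whether old baseline tests contributed. The article plans a range of control cohorts to show how much results depend on control selection, but test recency is not among the dimensions varied.

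**Working it through.** The plan gives no figure on this point to reproduce. The check is a comparison of texts, followed by two calculations on assumed inputs.

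**1. Does any stated analysis tighten test recency?**

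| Control set | Kidney-test requirement | Limit on age of test |
|---|---|---|
| Primary | one normal result, no abnormal value | 10 years before index |
| Group i | one normal result | none restated |
| Group ii | none; known abnormal excluded | not applicable |
| Group iii | none; known abnormal excluded | not applicable |
| Group iv | earlier studies' matching rules | not stated |
| At least 5 years of history | a condition on record length | none added |

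The last row needs care. Take a control aged 40 with a normal dipstick at 31, none since, and no exclusionary diagnosis. That control meets the kidney criterion of the primary set and of groups i to iii, and has 9 years of history. If history runs from the first record, the subset keeps every control whose test is 5 to 10 years old. It drops only short records, whose tests are necessarily less than 5 years old. It cannot serve as a recency check.

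**2. Do the safeguards close the gap?**
- Exclusionary diagnoses count up to 1 year after index (Initial matching algorithm). This helps only where disease is coded, and the pilot study found abnormal creatinine and urine protein underdiagnosed.
- Every chart is reviewed for raised creatinine, proteinuria and hypertension. This finds abnormal results where tests exist, not where none was done.
- Any abnormal value of the three tests disqualifies. The same limit applies.
- The nearest laboratory values before and after index are abstracted. No stated rule uses the later value or the interval.
- Non-kidney cancer is a negative-control outcome. It can signal poor control selection in general, but is not specific to undetected kidney disease.

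**3. Illustration of direction.** The inputs are assumptions, not document figures. Suppose a fraction f of controls has undetected disease with r times the outcome hazard, and donors have none. Then approximately

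observed HR = true HR / (1 + f(r − 1)).

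For a true HR of 1.20 and r from 2 to 5:
- f = 1%: 1.20/1.01 = 1.19 down to 1.20/1.04 = 1.15
- f = 2%: 1.20/1.02 = 1.18 down to 1.20/1.08 = 1.11
- f = 5%: 1.20/1.05 = 1.14 down to 1.20/1.20 = 1.00

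This shows which way the bias runs and how it scales. It does not estimate f or r.

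**4. Precision of a recent-test cohort.** Minimal detectable HR = exp[(1.960 + 0.842)/√(D/4)] for 1:1 matching, two-sided 5% (sidedness is not stated), 80% power, where D is total events.
- Reproducing the Power section, mortality: D = 7057 × 0.98 × 2 × 0.11 = 1521, giving 1.15 (stated 1.16). For eGFR < 45: D = 4022 × 0.98 × 2 × 0.08 = 631 and, at 14%, 1104, giving 1.25 and 1.18 (both as stated).
- If 50% of donors keep a recently tested control (assumed): 1.23 for mortality, 1.27 to 1.37 for eGFR < 45.
- If 25% do (assumed): 1.33 and 1.40 to 1.56.

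**The case against.** The strongest reply is that the authors saw the trade-off and chose deliberately. The article says that requiring laboratory data may select people tested because disease was suspected, and that young healthy controls often lack creatinine. A short window could exchange one bias for another. This stands, and it is why the primary definition should not change. It does not explain why the window is never varied, or why the text says index date.

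The safeguards are real, and baseline windows and interval reporting are often left to an analysis plan. But here the article itself states the window, and that window conflicts with its own claim.

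Three stronger readings are tempting and are not supported:
- *Every REP-based sensitivity set is broader than the primary one.* The subset with at least 5 years of history is narrower, and group iv is not shown to be broader.
- *BMI and blood pressure may be equally old, which would hide imbalance beyond the 0.1 tolerance.* The 10-year phrase most naturally governs the kidney tests only. Values nearest to index are abstracted, and the article reports that more than half of the population is examined each year. Any figure would need drift rates and intervals that the documents do not give.
- *Donor risk is therefore understated on balance.* Controls must also have an encounter at least a year after index and no exclusionary diagnosis in that first year. This favours healthier, surviving controls and pushes the other way.

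**Conclusion.** The point holds as a mismatch between rule and claim, together with a missing recency check. A single normal result up to 10 years old qualifies a primary control. The article describes such controls as normal at the index date. Nothing stated tests whether older results admit controls with undetected kidney disease.

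The direction from this source alone is toward or below a hazard ratio of 1, assuming that undetected disease raises control event rates and that donors, evaluated at donation, have less of it. The size cannot be derived from the documents, and the net bias across all selection steps is not established. The conclusion concerns the kidney tests. It does not extend to BMI or blood pressure, and it does not make the primary definition wrong.

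**What to change.** Keep the primary definition, and make three changes:

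1. Add one cohort to Control groups for sensitivity analysis: controls meeting the primary criteria whose qualifying kidney test falls close to index, for example within 3 years before it. Three years is a suggestion; the limit should be fixed before outcomes are compared.
2. Report the distribution of test-to-index intervals for the primary controls. The 10-year rule cannot be applied without test dates, so these should already be held.
3. In the Background and Discussion, describe the controls as normal on testing within 10 years before index.

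The cost is one further match and analysis from values already abstracted. The downsides are fewer controls, wider intervals (as in the precision calculation above), and possible selection of people tested on suspicion of disease. The documents do not show how many controls have a recent kidney test: the reported 85–100% contact over 3 years concerns visits, not kidney tests. The cohort is therefore a sensitivity analysis only, and a difference from the primary result should be read with the selection problem in mind.

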**Baseline characteristics**		
Demographics	CR	CR^1^
History of substance abuse^2^	CR	CR
Diagnosis of Depression/Anxiety Disorder^3^	CR	CR
High cholesterol	CR, SS	CR, SS
Hypertension^4^	CR, SS	CR, SS
Family history of kidney disease, DM, HTN	CR, DS, SS	CR, SS
Smoking history	CR, DS, SS	CR, SS
**Lab measurements**	Requested every 3 years with study survey	Recorded every year if available
BUN/Urea	CR	CR, LD
Glucose	CR	CR, LD
Urine protein^5^	CR	CR, LD
BMI	CR, DS, SS	CR, LD, SS
Creatinine	CR, DS, SS	CR, LD, SS
Blood pressure	CR, DS, SS	CR, LD, SS

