#### Survey data: mortality, ESKD, and other outcomes

UMN donors and validated REP controls not known to be deceased will be sent a standardized survey to determine outcomes. This survey is based on the existing survey that has been used for UMN donors, but modified to be usable with both LDs and controls. This survey supplements the capture of key data that may not be consistently documented in the medical record with specific items including: hematuria or proteinuria of at least 6 months duration, hypertension, DM, heart failure, myocardial infarction, angioplasty or stent, angina, smoking history, and pregnancy history; and family history of hypertension, DM, or ESKD (see **Supplemental Materials** for the survey). We will additionally capture cancer information to use as a negative control (see statistical analysis section).

The survey will allow for uniform ascertainment of outcomes between UMN donors and REP controls. Because Mayo LDs have not been routinely contacted about health outcomes after donation, they do not have a similar long-term follow-up history as UMN LDs from which to validate survey responses. Because of this and budgetary constraints, only the REP controls and UMN donors will be surveyed.

UMN donors will be contacted to complete the survey using a similar process as described previously for the 3-year postdonation follow-up surveys. Data obtained from this new survey will be used to supplement data collected in the triannual surveys sent to UMN donors previously.

For REP controls, mailing addresses and phone numbers will be obtained from recent Olmsted County medical care episodes. REP controls without a recent medical visit will be queried in Accurint™ to determine if they are alive and if so, identify their most recent mailing address and phone number. Up to three mailed surveys, with the first including an incentive item for participation, will be sent to the controls followed by up to 5 phone calls (including evenings and weekends). After surveying the first validated control for each REP donors, we will prioritize surveying controls for donors who lack completed surveys by a matched control.

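### Family history taken from a survivors-only survey can select the primary matched controls on survival and inflate the donor hazard ratio for death

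*Protocol article*

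**What the plan says.** Under Primary control group and matching algorithms, the primary cohort consists of those where "we consider controls for whom we can ascertain BMI, systolic and diastolic blood pressure, use of anti-hypertensive medications, smoking history" and normal kidney tests are available. The team will also try to include "family history of CKD at the index date (either through chart review or from survey results) as a factor in the matching". If too few controls have a matching characteristic, the article falls back on multivariable adjustment for it.

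Under Survey data, "UMN donors and validated REP controls not known to be deceased will be sent a standardized survey to determine outcomes". Before mailing, "REP controls without a recent medical visit will be queried in Accurint™ to determine if they are alive". On its purpose: "This survey supplements the capture of key data that may not be consistently documented in the medical record". The listed items include smoking and "family history of hypertension, DM, or ESKD". After a first validated control per donor has been surveyed, "we will prioritize surveying controls for donors who lack completed surveys by a matched control".

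Table 2, in the row "Family history of kidney disease, DM, HTN", gives chart review and study survey as sources for controls, and chart review, donor survey and study survey for UMN donors. Smoking history has the same sources.

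Under Statistical analyses details, time-to-event outcomes run from the index date. No later entry is described for controls classified by survey.

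**The concern.** Matching on a baseline variable is harmless only if knowing that variable does not depend on the outcome. Here it can. Take two identical controls with nothing about family history in the chart. One dies ten years after index; the other lives to return the survey. Only the second can be matched on family history. The death of the first is still obtainable, because all REP controls go to the National Death Index; only the covariate is missing.

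Donors enter whether or not they later die. In Table 1 the relationship to the recipient is unknown for 0% of UMN and 0.4% of Mayo donors. The selection therefore acts almost entirely on one arm, and it makes donation look harmful for all-cause mortality. The same direction is probable for ESKD and cardiovascular outcomes, which shorten life. It is less certain for other outcomes.

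The stakes are high because the article expects only small differences and plans a public risk calculator for candidate donors.

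**Working it through.** **1. The study's own benchmark.** Inputs from Power and Table 1: 4022 + 3035 = 7057 donors, 98% matched, 11% deaths, type I error 5% (two-sided assumed), power 80%. With k controls per donor, D = 0.98 × 7057 × (1+k) × 0.11 and a = 1/(1+k), Schoenfeld's formula gives HR = exp[(1.960 + 0.842)/√(D·a·(1−a))].

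- 3:1: D = 3043, HR = 1.124 (stated 1.13).
- 1:1: D = 1521, HR = 1.154 (stated 1.16).

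The stated figures are these values rounded up, so they are a fair yardstick.

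**2. Spurious hazard ratio with no true effect.** Let true mortality be 11% in both arms, and let a share s of matched controls be classified only by survey. Those controls cannot have died before the survey. If follow-up ends soon after it, control mortality is 11% × (1−s), and HR = ln(0.89)/ln[1 − 0.11(1−s)], which is close to 1/(1−s).

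| s (assumed) | Control deaths | HR, log formula | 1/(1−s) |
|---|---|---|---|
| 5% | 10.45% | 1.06 | 1.05 |
| 10% | 9.9% | 1.12 | 1.11 |
| 20% | 8.8% | 1.27 | 1.25 |
| 50% | 5.5% | 2.06 | 2.00 |

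The shares that alone produce the detectable ratios are 1 − 1/1.13 = 11.5% and 1 − 1/1.16 = 13.8%.

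**3. Check with age adjustment.** This was a simulation with true HR 1 and Gompertz mortality calibrated to 11% deaths. Index decades and approximate ages came from Table 1, the survey response was assumed to be 40% or 60%, and a Cox model adjusted for age.

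| s | Simulated HR | Chart-classified controls only | 1/(1−s) |
|---|---|---|---|
| 10.6% | 1.13 | 1.03 | 1.12 |
| 15.2% | 1.15 | 1.01 | 1.18 |
| 26.0% | 1.27 | 0.98 | 1.35 |
| 34.7% | 1.42 | 0.99 | 1.53 |
| 51.5% | 1.92 | 1.02 | 2.06 |

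The chart-only column should be 1, so simulation noise is about 0.03. At larger shares the simple formula runs somewhat high.

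**4. Is s likely to be more than trivial?** From Table 1, donors who are a child, parent, full sibling or identical twin of the recipient number 474 + 932 + 1579 + 15 = 3000 of 4022 (74.6%) at UMN and 493 + 422 + 934 + 5 = 1854 of 3035 (61.1%) at Mayo. Matching them takes many controls with a positive family history, while chart abstraction records only what the notes happen to mention. The pressure to use survey answers is real. The share itself is not stated.

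**The case against.** **The design already varies the control group.** Sensitivity groups i to iii drop family history, group iii also drops smoking, and incidence is estimated in every group. A survival artefact from family history should show as lower control mortality in the primary group. The cancer negative control is meant to expose biased control selection. This stands as a means of detection. It does not correct the primary estimate, and a gap between the primary group and group i could be misread as confounding by family history. Standardized differences compare baseline values and cannot show selection on later survival. The adjustment fallback uses the same variable.

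**Donors' family history also has survey sources.** True for UMN, and relationship does not settle family history for the unrelated and spousal donors: (562 + 198)/4022 = 18.9% at UMN and (662 + 327)/3035 = 32.6% at Mayo. So donors are largely, not wholly, free of the condition.

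**Some stronger readings are tempting but unsupported.**

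- A reader might infer that controls without a known family history are excluded. The article calls it a matching factor that it will attempt to include, not an eligibility criterion.
- A reader might infer that the survey asks about relatives as of today. The form is in the supplement, which is not shown, so its time frame cannot be judged.
- A reader might infer from Table 2 that smoking, hypertension and cholesterol certainly enter the primary cohort by survey. Table 2 lists data sources, not eligibility rules, and cholesterol is not a matching variable. For smoking the route is possible but unclear, since the ten-year pre-index window could be read as covering it, although it attaches more naturally to the kidney tests.

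**A condensed article may leave delayed entry to the full plan.** That is fair as to its absence. The article does, however, positively name the survey as a source for primary matching.

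**Conclusion.** The point holds for controls whose family history of CKD is known only from the survey, and for smoking if the survey is used to meet that criterion. The direction is clear for all-cause mortality: against donation.

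The size depends on an unstated share. At 5% the spurious ratio is about 1.06, and at 10 to 11% it is about 1.12 to 1.13, comparable with the effects the study is powered to detect. Larger values such as 2.06 need half the matched controls to be survey-only, which nothing in the article establishes.

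The figures assume no true effect, equal underlying mortality, a survey near the end of follow-up, and that a known family history makes a control more likely to be matched. A reader might picture up to 60 guaranteed years for controls generally. It concerns survey-only controls, and 2469 of 4022 UMN donations (61.4%) and 2501 of 3035 Mayo donations (82.4%) date from 1990 to 2012, so the guaranteed span is often much shorter.

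**What to change.** For every time-to-event analysis, base primary eligibility and matching on information recorded independently of survival to the survey: chart entries at or before index, with a not-documented level for family history and smoking. Mark the study survey in Table 2 as a supplementary source for these baseline items in controls.

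Keep the survey information, because discarding it could bring back the family-history confounding that the study was designed to remove. There are two sound ways:

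- **Delayed entry.** Controls classified by survey join the risk set at the survey date. This is free of the bias but adds little person-time if follow-up ends soon afterwards.
- **Multiple imputation.** Impute family history for all controls, living or dead, with chart and survey answers as inputs and vital status and follow-up time in the model.

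Report the survey-only share among matched controls, overall and by index decade, so that readers can gauge the exposure.

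The cost is revised wording, a repeat of the match and one added analysis. Fewer controls will have a directly known family history, and some confounding by it will remain, which the imputation or delayed-entry analysis should address.
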